#### Long-term outcomes after hospital discharge

Neurodevelopmental impairment at 104 weeks corrected age: The Bayley Scales of Infant and Toddler Development, Second Edition (BSID II) will be used in this trial.
Cognitive delay: defined as a cognitive score less than 80.Language delay: defined as a language score less than 80.Cerebral palsy and severity of cerebral palsy using the gross motor function classification system.Hearing loss requiring hearing aids at 104 weeks corrected age.Blindness at 104 weeks corrected age: vision loss with only form or shadow vision or no useful vision.Number of readmissions in the first year since the first discharge home.Weight, length, and head circumference at 40 weeks postmenstrual age and 12, 26, 52, and 104 weeks corrected age.Premature birth-related mortality from enrollment to 104 weeks corrected age.Behavioral problems (child behavior checklist) at 104 weeks corrected age. The scores on the checklist will be compared between groups.

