## Abstract

**Background:**

Bronchopulmonary dysplasia (BPD) is still a common complication in very premature infants. At present, there is no effective treatment for BPD. Glucocorticoids are drugs commonly used to prevent or treat BPD before and after birth. In very premature infants with high risk factors for BPD, early use of dexamethasone can reduce the rate of death and/or BPD but may cause long-term adverse neurodevelopmental outcomes. Hydrocortisone (HC), as an alternative drug to dexamethasone, has been increasingly used to prevent BPD. However, no study has reported the efficacy and safety of HC to treat early BPD diagnosed at postnatal day (PND) 28.

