**Methods:**

This study protocol is for a multicenter double-blind randomized controlled trial of low-dose HC in the treatment of early BPD. Early BPD infants will be randomly assigned to the HC treatment group or control group. Infants in the HC group will receive 0.5 mg/kg HC twice a day for 7 days and then 0.5 mg/kg HC once a day for 3 days. The control group will be given the same volume of placebo and no intervention on the basis of routine treatment. The primary outcome is survival without moderate or severe BPD at 36 weeks postmenstrual age. Secondary outcomes are the short- and long-term effects on growth, metabolism, neurodevelopment, and other possible complications.

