### Clinical data collection

At the time of randomization, baseline data will be collected from all included patients, including maternal and patient characteristics. Demographic data will include sex, birth weight, gestational age, 5-min Apgar score, surfactant therapy, prenatal corticosteroid use, premature rupture of the membrane before the onset of labor (> 18 h), singleton/multiple birth, and mode of delivery. Population characteristics will be used to compare outcomes between the two groups.

The following clinical data will be collected: continuous positive airway pressure (CPAP)-assisted time, invasive ventilator-assisted time, days of hospitalization, days on supplemental oxygen, IVH, spontaneous intestinal perforation, NEC, and ROP.

During HC treatment, respiratory support, blood sugar, blood pressure, and anthropometric data will be collected. Outcome variables and cointerventions will be recorded at 36 weeks PMA.

After discharge, one trained investigator in each center will follow up all patients at 40 weeks PMA and at 12, 26, 52, and 104 weeks corrected age. We will provide free neurodevelopmental impairment examinations to promote follow-up rates. For potential dropouts during the follow-up, we will expand the sample size by 20% and the missing data will be ignored in the analysis. The outcomes at each time point mentioned above will be collected by the investigators (Table 1).

**Table 1 Tab1:** SPIRIT figure: showing time points for enrollment, interventions, and assessment

	Study period						
	Enrollment	Allocation	Post-allocation				Close-out
Time point	At 4 weeks after birth	At 4 weeks after birth	At 36 weeks postmenstrual age	At 40 weeks postmenstrual age	At 12, 26 weeks corrected age	At 52 weeks corrected age	At 104 weeks corrected age
Enrollment:							
Eligibility screen	X						
Informed consent	X						
Demographic data	X						
Allocation		X					
Intervention:							
Hydrocortisone		X					
Placebo		X					
Assessments:							
Baseline variables assessments	X	X					
Primary outcome			X				
Secondary outcomes:							
Brain volume				X			
Others			X				
Long-term outcomes:							
Neurodevelopmental impairment, hearing loss, and blindness							X
Number of readmissions						X	
Weight, length, and head circumference				X	X	X	X
Behavioral problems, premature birth-related mortality							X

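### The 104-week definitions of cognitive delay and language delay do not fit the Bayley edition that the protocol names

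*Protocol article*

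**What the plan says.** The section on long-term outcomes after hospital discharge names one instrument for neurodevelopmental impairment at 104 weeks corrected age: "The Bayley Scales of Infant and Toddler Development, Second Edition (BSID II) will be used in this trial". Two score-based definitions follow: "Cognitive delay: defined as a cognitive score less than 80" and "Language delay: defined as a language score less than 80". The next item is "Cerebral palsy and severity of cerebral palsy using the gross motor function classification system". Hearing loss and blindness are listed after that.

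Table 1, under Clinical data collection, places "Neurodevelopmental impairment, hearing loss, and blindness" at the close-out visit. The Methods paragraph of the abstract gives these outcomes secondary status: "Secondary outcomes are the short- and long-term effects on growth, metabolism, neurodevelopment, and other possible complications".

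The article mentions no other Bayley edition, no mental or psychomotor index, no separate language test, and no rule for turning one set of scores into another.

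**The concern.** The protocol fixes both the edition of the test and the scores to be read from it, and the two do not appear to belong together. As generally understood, the Second Edition pools cognition and language into one mental index beside a psychomotor index. Separate cognitive and language composites came with a later edition. If so, an assessor using the named edition obtains no number to set against either cut-off.

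The subject matter gives this weight. The abstract's Background says that early dexamethasone "may cause long-term adverse neurodevelopmental outcomes". The Background and Discussion present low-dose hydrocortisone as an alternative expected to avoid that harm, and the stated aim covers safety as well as efficacy. The two affected definitions are the only ones in the article that would show cognitive or language delay on a developmental test.

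**Working it through.** No arithmetic tests this point. The sample size is built on moderate or severe BPD, and no stated figure depends on the Bayley. The check sets each definition against the named instrument.

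**Inputs from the document**
- Instrument: Bayley, Second Edition, with the abbreviation BSID II.
- Definition A: cognitive score below 80.
- Definition B: language score below 80.
- Other 104-week items: cerebral palsy with graded severity, hearing loss needing aids, blindness, the behaviour checklist.

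**Premise from outside the document (assumption).** The Second Edition reports a mental index, a psychomotor index and a behaviour rating, with no separate cognitive or language composite. The article neither states nor contradicts this, so the test manual must settle it.

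**Match, item by item, under the premise**

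| Item | Score needed | Available from the named edition? |
|---|---|---|
| Cognitive delay | Separate cognitive score | No; cognition is pooled in the mental index |
| Language delay | Separate language score | No; language is pooled in the mental index |
| Cerebral palsy and severity | Diagnosis and motor grading | Does not use the Bayley |
| Hearing, vision | Clinical findings | Do not use the Bayley |
| Behaviour | Checklist score | Does not use the Bayley |

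So 2 of the 2 Bayley-based definitions fail, and none of the other items does.

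**How the conclusion depends on the premise**
- If the premise is right, neither definition can be scored as written. Using the pooled index for both would not help: both definitions would become the same comparison (mental index below 80), and the two delay rates would be equal by construction. The protocol does not propose this; it only shows that the text cannot be rescued by substitution.
- If the manual shows that the Second Edition does give separate standardised cognitive and language scores, the definitions can be applied and the point falls away, apart from the value of naming those scores.

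**Is it resolved elsewhere?** The sections on clinical data collection, statistical analysis and quality control, and Table 1, add no edition, index or mapping. One internal sign suggests a mixing of editions: the spelled-out title includes toddlers, while the abbreviation has no letter for them. This is weak evidence and the point does not rest on it.

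**The case against.** The strongest objection is that the mismatch is not visible in the article alone. The text names a test and two cut-offs, and only knowledge of how the test is scored makes them conflict. This stands as a limit on certainty, and it is why the premise is labelled. It does not remove the point: the scoring structure belongs to the instrument the protocol itself chose, and can be looked up.

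A second objection is that a journal article leaves test administration to the full protocol. That would answer a missing detail. Here the article states both an edition and the scores, and a fuller document cannot draw a language score from a test that does not give one.

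Several stronger readings are tempting, and the document does not support them:
- *The main safety outcome is lost.* The protocol ranks no long-term outcome above another, and the abstract makes them all secondary.
- *Neurodevelopment cannot be assessed.* Cerebral palsy with severity, hearing, vision and behaviour can be, as can the in-hospital brain measures.
- *Each centre will improvise its own scoring.* Nothing says so. Quality control provides for training all researchers in standard procedures, and one trained investigator per centre does the follow-up. Divergence is possible, but a guess.
- *All 196 infants are affected.* That total already includes the 20% allowance for dropout. The number before inflation is 81 × 2 = 162, and the number actually tested at 104 weeks is unknown.
- *Failing to use a motor score is an error.* A graded motor measure is planned through cerebral palsy severity. Milder motor delay has no cut-off of its own, but adding one is a design preference.

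**Conclusion.** The concern holds in a limited form. Given the premise about the Second Edition's scoring, the cognitive-delay and language-delay definitions cannot be applied as written, for any child assessed with the named edition. The effect stops at those two secondary endpoints: the primary outcome, its analysis and the sample size do not change.

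The finding ranks below a must-fix because the outcomes are secondary and a wording change can put them right. It should still be corrected, because it affects the only test-based cognitive and language endpoints in a trial motivated by long-term neurodevelopmental harm, and a child tested with an unsuitable edition cannot later be retested at the same age. The document gives no basis for estimating how delay rates would differ between editions or indices, so no numerical size is offered.

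**What to change.** First confirm in the test manual which scores the named edition reports. Then make edition and scores match, identically in all three centres, before the first 104-week visit. Either route works:

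1. **Name the edition that yields separate cognitive and language composites** and keep both definitions. This preserves the endpoints as conceived. It may require a different test kit.
2. **Keep the Second Edition**, restate the score-based definition on its mental index, state the cut-off for that scale rather than carrying 80 over unexamined, and drop the separate language endpoint. This needs no new instrument or visit; the cost is the loss of the language endpoint.

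A psychomotor or motor cut-off may be added under either route, but it is optional and not part of this correction.

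There is time to do this. The most mature eligible infant (30 weeks 6 days at birth) is about 34 weeks 6 days at randomization on day 28. That leaves 5 weeks 1 day to 40 weeks, then 104 weeks of corrected age, so the earliest visit falls about 109 weeks after the first randomization. Under the article's own rule on protocol changes, the amendment would need ethics committee approval and new written consent from guardians.

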**Discussion:**

This trial will determine the efficacy and safety of low-dose HC administration compared to placebo for the reduction of moderate or severe BPD at 36 weeks postmenstrual age in very preterm infants with early BPD.

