### Sample size calculation

According to the data from the participating centers in the past 2 years and the data presented from the range of previous studies [27–29], the incidence of early BPD in infants with gestational age 26^+0^ to 30^+6^ weeks was 68–77%, and 40% developed moderate or severe BPD. The effect of HC therapy was assumed to reduce moderate or severe BPD (the primary endpoint) to 25% or less (number needed to treat, NNT = 5). Adopting a maximum significance level of *α* = 0.05 and a minimum test power of 80%, the number of subjects per group will be *N* = 81, which will be increased by 20% to compensate for potential dropouts during the follow-up, leading to 98 subjects per group (total 98 × 2 = 196 subjects).

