### Statistical analysis

The analyses will be based on the intention-to-treat (ITT) principle in accordance with the Consolidated Standards of Reporting Trials (CONSORT). Statistical analyses will be performed with SAS version 9.2 (SAS Institute, Cary, North Carolina). Data will be presented as the mean ± standard deviation or median and interquartile range depending on their distribution. Categorical data, including the primary outcome, will be analyzed using the chi-square test between two groups. Continuous data will be analyzed using Student’s *t* test or the Mann-Whitney test as appropriate. The effect of HC on the dichotomous outcomes will be assessed by multivariable logistic regression analysis including possible confounders, including birth weight and gestational age. Statistical results will be reported as point estimates and 95% confidence intervals.

Mid-term data analysis will be conducted after inclusion of the first 98 patients. The principal investigator will decide whether any measure should be taken in light of the results. Case report forms (CRFs) will be entered by two independent researchers to ensure accuracy.

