## Discussion

In babies < 26^+0^ weeks gestational age, several problems, such as PDA, severe apnea, and high thorax compliance, may lead to noninvasive respiratory dependency at day 28 without any link to BPD. Furthermore, a higher rate of sepsis was observed in infants born at 24–25 weeks gestational age who were treated with hydrocortisone in a previous study [21]. Therefore, we will restrict the eligible patients to those between 26^+0^ and 30^+6^ weeks gestational age.

Because inflammation plays a key role in BPD, postnatal glucocorticoids are thought to be the most effective therapeutic strategy for preterm infants with a high risk for developing BPD [35], but they are accompanied by severe long-term adverse neurodevelopmental outcomes [11, 12]. These adverse outcomes seem to be associated with the timing of steroid exposure and the cumulative dosage of glucocorticoids; the earlier the treatment initiation and/or the larger the dosage, the higher the risk of adverse outcomes [11, 15].

Following the actual recommendations, many infants presenting with early BPD do not receive any anti-inflammatory therapy, and a high percentage of premature infants are still oxygen-dependent or on respiratory support at 36 weeks PMA (moderate or severe BPD) [27–29], which is associated with poor long-term pulmonary outcomes, including home oxygen therapy and a high rate of bronchopulmonary infections and rehospitalization [2]. A recent study showed that moderate or severe BPD at 36 weeks PMA was associated with increased mortality in the first year of life and moderate to severe neurodevelopmental impairment (55%) [6]. Thus, we hypothesize that anti-inflammatory treatment of infants meeting the NICHD criteria for BPD at 28 days of life may decrease the incidence of moderate or severe BPD at 36 weeks PMA and reduce long-term adverse outcomes.

In previous studies, early low-dose HC therapy in ventilator-dependent infants improved the rate of survival without BPD at 36 weeks PMA [21] without adverse neurodevelopmental outcomes at 2 years of age [22, 24]. Thus, it seems reasonable to use low-dose HC to treat infants with early BPD to improve pulmonary outcome. Accordingly, the efficacy and safety of this treatment must be proven by a randomized controlled trial.

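### The 104-week cognitive and language scores are analysed only as delay below 80, which gives up much of the power to see a general shift, while safety is said to be determined and proven

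*Protocol article*

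**What the plan says.** **Aim.** The abstract's Discussion states: "This trial will determine the efficacy and safety of low-dose HC administration compared to placebo". The Aim of the study also names efficacy and safety, and the main Discussion says that "the efficacy and safety of this treatment must be proven by a randomized controlled trial". The Background, the dosing section and the Discussion all present adverse long-term neurodevelopment as the main concern with postnatal steroids.

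**Outcomes.** Under Long-term outcomes after hospital discharge, two of the 104-week results are cut at a threshold: "Cognitive delay: defined as a cognitive score less than 80" and "Language delay: defined as a language score less than 80". In the same list the behaviour checklist is left uncut: "The scores on the checklist will be compared between groups".

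**Analysis.** Under Statistical analysis: "Categorical data, including the primary outcome, will be analyzed using the chi-square test between two groups". Dichotomous outcomes also get a multivariable logistic regression that includes birth weight and gestational age. Continuous data get a t test or Mann-Whitney test. Results are to be given as point estimates with 95% confidence intervals.

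**Size.** The sample size rests on the respiratory endpoint alone: "The effect of HC therapy was assumed to reduce moderate or severe BPD (the primary endpoint) to 25% or less". It gives 81 per group, raised to 98. No harm margin is stated for any outcome.

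**The concern.** A shift in developmental score across the whole treated group is a plausible form of steroid harm. A count of children below 80 registers such a shift only through those who cross the line; movement elsewhere on the scale is not counted. The article already names methods for continuous data and applies score comparison to behaviour, but not to the two scores closest to its stated worry.

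At stake is how much the trial can say about the question that makes hydrocortisone contentious. A comparison that often fails to show a moderate harm, set beside wording about determining and proving safety, invites a stronger conclusion than the data would carry.

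**Working it through.** **The plan's own figure.** 98 is 81 × 1.2 = 97.2, rounded up. The 81 matches 40% against 20%, which is what a number needed to treat of 5 implies (82 by the pooled formula, 81 by arcsine). The stated 40% against 25% would need 152 per arm. That is a separate matter; only the numbers per arm are used below.

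**Inputs from the article**
- 98 per arm enrolled. A 20% loss leaves 98 × 0.8 ≈ 78.
- Cut at 80, and a chi-square test. α = 0.05, taken as two-sided because the sides are not stated.
- Missing data are ignored, so the analysis uses the children seen.

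**Assumptions, not in the article**
- Scores are normal with SD 15, and the control mean m is 85, 90, 95 or 100.
- Harm is a uniform loss of 7.5 points (half an SD).

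**Step 1: rates below 80.** Control rate = Φ((80 − m)/15). Hydrocortisone rate = Φ((87.5 − m)/15).

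**Step 2: power of the chi-square test.** This sums the binomial probabilities of all pairs of counts for which |p̂₁ − p̂₂| / √(p̄(1 − p̄)·2/n) > 1.96 (no continuity correction).

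| Control mean | Below 80: control → HC | Power, 78/arm | Missed | Power, 98/arm | Missed |
|---|---|---|---|---|---|
| 100 | 9.1% → 20.2% | 51.5% | 49% | 60.6% | 39% |
| 95 | 15.9% → 30.9% | 61.0% | 39% | 71.1% | 29% |
| 90 | 25.2% → 43.4% | 67.7% | 32% | 76.6% | 23% |
| 85 | 36.9% → 56.6% | 68.4% | 32% | 80.1% | 20% |

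**Step 3: the same children compared on the score.** The t test has noncentrality 0.5·√(n/2).
- 78 per arm: 0.5·√39 = 3.12 on 154 df, power 87%, missed 13%.
- 98 per arm: 0.5·√49 = 3.50 on 194 df, power 94%, missed 6%.

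**Step 4: a different shape of harm.** Suppose instead that 15% of treated infants lose 30 points and the rest lose none, an average loss of 0.15 × 30 = 4.5 points. Simulated power at 78 per arm:

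| Control mean | t test on score | Chi-square on below 80 |
|---|---|---|
| 100 | 38% | 44% |
| 95 | 38% | 35% |
| 90 | 38% | 27% |

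Here the score's advantage shrinks, and at mean 100 it reverses. Neither analysis is strong. This favours reporting both rather than replacing one with the other.

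**Step 5: what the intervals could exclude.** At 78 per arm the 95% interval on a mean difference has half-width 1.96 × 15 × √(2/78) = 4.7 points. If there is no true difference, the chance that it excludes a 7.5-point loss is Φ(7.5/(15·√(2/78)) − 1.96) = Φ(1.16) = 88%. For a loss of one third of an SD the chance is 55%.

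For yes/no harms in general, with control rates of 10%, 20% and 30% (again assumed), the half-width 1.96·√(2p(1 − p)/78) is 9, 13 and 14 percentage points. The power to detect a 10-point rise is 43%, 31% and 27%.

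**The case against.** The strongest reply has five parts.

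- **No rule equates p > 0.05 with safety.** A reader might infer that the trial would call hydrocortisone safe on a non-significant chi-square test. The article does not say so, and it plans point estimates with 95% confidence intervals, which show how much harm remains possible. This stands: misreading is a risk of interpretation, not an error in the plan.
- **Chi-square is not the only analysis.** An adjusted logistic regression is also planned. This stands, and the miss rates above describe the unadjusted test only. But the regression uses the same dichotomised outcome, so it does not recover the information lost at the cut.
- **These are not the only neurodevelopmental outcomes.** The article also lists cerebral palsy with severity, hearing loss, blindness, the behaviour score, brain volume, sleep-wake maturation and head circumference, and several of these are continuous. A reader might infer that neurodevelopmental safety hangs on the cut scores alone; it does not.
- **The safety promise is limited.** The abstract sentence goes on to refer to BPD at 36 weeks, the Aim says only that safety will be investigated, and long-term effects are secondary. Sizing a trial on its primary endpoint is normal, and a margin may properly be left to an analysis plan not shown. This stands as to the margin. The Discussion nevertheless speaks of proof, and the cut at 80 and the test family are fixed in the article itself.
- **The figures depend on the harm model.** This stands, as Step 4 shows. Delay below a threshold is also a recognisable clinical endpoint, which is a reason to keep it.

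**Conclusion.** The point holds as a mismatch between aim and method. Neurodevelopment is the article's main concern with postnatal steroids, yet its cognitive and language results are specified only as proportions below 80. For a uniform half-SD loss this raises the chance of missing the harm from 13% to 32–49% at 78 per arm, and from 6% to 20–39% at 98. These figures rest on SD 15, control means of 85 to 100, normal scores and a uniform shift, none of which the article gives. For harm confined to a few infants the advantage can disappear.

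The documents do not support saying that the trial will declare safety from a non-significant test, or that the absence of a margin is itself an error. What they support is a modest, inexpensive addition to the stated analysis and more careful safety wording.

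**What to change.** 1. In Long-term outcomes and Statistical analysis, add the difference in mean cognitive and language score at 104 weeks corrected age, with a 95% confidence interval, adjusted for gestational age and birth weight.
2. Keep the below-80 proportions alongside it, reported as risk differences with 95% confidence intervals.
3. In the abstract's Discussion and the main Discussion, replace the language of determining and proving safety. Say that neurodevelopmental and rarer harms are estimated, and that conclusions are limited to the harm the 95% interval excludes.
4. A formal non-inferiority margin is optional and for the sponsor to choose, before unblinding. The half-SD figure used above is an illustration, not a recommendation.

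Cost: one extra secondary analysis and a more modest safety claim. No additional infants or visits are needed, since the scores come from the 104-week assessment already planned.

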### Outcomes

#### Primary outcome

The primary outcome is survival without moderate or severe BPD at PMA 36 weeks, which is defined as the following criteria: no respiratory support, spontaneous breathing FiO_2_ 0.21 for SpO_2_ 92%.

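### Cognitive and language delay at two years need a test score, so infants who died or were too impaired to be tested drop out of these two comparisons although their status is known and adverse

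*Protocol article*

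**What the plan says.** All references are to the protocol article.

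- **Long-term outcomes after hospital discharge.** The instrument and time are fixed: "Neurodevelopmental impairment at 104 weeks corrected age: The Bayley Scales of Infant and Toddler Development, Second Edition (BSID II) will be used in this trial". Two items depend wholly on a score: "Cognitive delay: defined as a cognitive score less than 80" and "Language delay: defined as a language score less than 80". Cerebral palsy with its severity, hearing loss and blindness are listed as well, and none of them is defined by a Bayley score. Death is a separate item: "Premature birth-related mortality from enrollment to 104 weeks corrected age". No item combines death with impairment.
- **Clinical data collection.** After providing for dropouts by enlarging the sample by 20%, the text says that "the missing data will be ignored in the analysis".
- **Statistical analysis.** "The analyses will be based on the intention-to-treat (ITT) principle". Categorical outcomes go to a chi-square test, and dichotomous outcomes also to a logistic regression with birth weight and gestational age. No rule is given for death or for a child who cannot be tested.
- **Primary outcome.** Here survival is part of the definition: "The primary outcome is survival without moderate or severe BPD at PMA 36 weeks".

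**The concern.** A child who died before 104 weeks cannot have a score, and a child too impaired to be tested may have none. In both cases the outcome is known and bad, which makes this different from ordinary loss to follow-up. A definition that needs a score, joined to a rule that ignores missing data, restricts the comparison to children who are alive and testable. Treatment may affect both conditions. The Discussion links moderate or severe BPD, which hydrocortisone (HC) is meant to prevent, with higher first-year mortality and with neurodevelopmental impairment.

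Neurodevelopmental harm is also the article's stated worry about glucocorticoids. If HC kept very sick infants alive, delay among scored children could rise in the HC arm through survival alone. If HC caused deaths, the same comparison could flatter it. The mortality item would not fully make up for this, because deaths judged unrelated to premature birth fall outside it.

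**Working it through.** **Inputs from the article:** 98 per group; 20% allowance for dropout; moderate or severe BPD 40% in controls and 25% with HC (Sample size calculation); 55% moderate to severe impairment with moderate or severe BPD (Discussion). The article gives no death, untestable or delay rate and no power for the two-year outcomes, so there is no figure of its own to reproduce.

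**Assumed:** death rates of 2% to 10%; impairment b = 20% in infants who would survive in either arm, with no treatment effect on them; q = 55% in infants alive only because they were in the arm with fewer deaths (the Discussion figure, borrowed); 98 × 0.8 ≈ 78 assessed per arm; 10% to 33% of impaired children untestable.

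**1. Deaths.** Let m_hi and m_lo be the death rates in the arms with more and fewer deaths.

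- Survivor-only rate, arm with more deaths: b. Arm with fewer: [(1 − m_hi)b + (m_hi − m_lo)q] / (1 − m_lo).
- Death or impairment: m + (1 − m) × survivor-only rate.
- Worked case, 8% control and 4% HC: HC survivor-only = (0.92 × 0.20 + 0.04 × 0.55)/0.96 = 0.206/0.96 = 21.5%, against 20.0%. Death or impairment: control 0.08 + 0.92 × 0.20 = 26.4%; HC 0.04 + 0.206 = 24.6%.
- Yardstick: SE = √(0.200 × 0.800/78 + 0.215 × 0.785/78) ≈ 6.5 points.

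| Deaths, control / HC | Survivor-only, control / HC | HC − control | Death or impairment, control / HC | HC − control | Swing |
|---|---|---|---|---|---|
| 4% / 2% | 20.0% / 20.7% | +0.7 | 23.2% / 22.3% | −0.9 | 1.6 points, 0.25 SE |
| 8% / 4% | 20.0% / 21.5% | +1.5 | 26.4% / 24.6% | −1.8 | 3.3 points, 0.50 SE |
| 10% / 5% | 20.0% / 21.8% | +1.8 | 28.0% / 25.75% | −2.25 | 4.1 points, 0.63 SE |
| 5% / 8% | 21.1% / 20.0% | −1.1 | 25.05% / 26.4% | +1.35 | 2.5 points, 0.38 SE |

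In this model the survivor-only difference (arm with fewer deaths minus the other) is (m_hi − m_lo)(q − b)/(1 − m_lo), and the composite difference is −(m_hi − m_lo)(1 − q). They have opposite signs for any q between b and 1. A real treatment effect in the common survivors, if larger than these amounts, would override this.

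**2. Untestable children.** Impairment arising through BPD: 0.40 × 0.55 = 22.0% against 0.25 × 0.55 = 13.75%, a difference of 8.25 points. If a share u of impaired children is dropped, the observed rate is r(1 − u)/(1 − ru).

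- u = 0.10: 0.198/0.978 = 20.2% against 0.12375/0.98625 = 12.5%, difference 7.7 points.
- u = 0.33: 0.1474/0.9274 = 15.9% against 0.0921/0.9546 = 9.7%, difference 6.2 points.

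Here the difference shrinks but does not reverse.

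**3. Both together, as assumed counts on 98 per arm.** Control: 2 deaths, 2 untestable, 20 scored below 80. HC: 4, 4 and 18.

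- Scored children only: HC 18/90 = 20.0%, control 20/94 = 21.3%, difference −1.3 points.
- Untestable survivors scored as delayed: HC 22/94 = 23.4%, control 22/96 = 22.9%, difference +0.5.
- Death, untestable or delayed over all randomized: HC 26/98 = 26.5%, control 24/98 = 24.5%, difference +2.0.

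**4. Equal losses.** With 6 deaths, 4 untestable and 18 delayed in each arm, both comparisons show no difference (18/88 and 28/98 in each arm). In general, if the arms lose the same number, the scored-only and all-randomized differences share the numerator (delayed HC − delayed control) and so the sign.

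**The case against.** The strongest reply is that the sentence on missing data opens with dropouts during follow-up, and that deaths and untestable children are not dropouts. On that reading the article is merely silent about their coding, which a condensed article may leave to a fuller document. The reading is fair, but it does not remove the problem. The delay items are still defined only by a score below 80, so an unscored child either leaves the denominator or stays in it as not delayed. In the third calculation the latter gives HC 18/98 = 18.4% against control 20/98 = 20.4%, again on the side of HC. Whether a severely impaired child would receive a floor score cannot be told from the article; for deaths no such route exists.

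Three other objections stand and limit the point.

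- A reader might infer that the worst-affected children vanish from the safety assessment. They do not: cerebral palsy, hearing loss, blindness and mortality are separate outcomes.
- A reader might take these two items as the trial's main long-term safety comparison. The article does not rank its long-term outcomes.
- A reader might infer that a reversal is to be expected. It needs unequal losses, and every rate behind the examples is assumed. The infants enrolled are alive at day 28, off invasive ventilation and free of recent severe infection, and no death rate is given for them.

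**Conclusion.** The concern holds for the cognitive and language comparisons only. As defined, they exclude children whose outcome is known and adverse, for reasons that treatment may influence. Unlike the primary outcome, no two-year developmental measure includes death, and the mortality item is restricted by cause.

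The size is modest: a shift of about 0.25 to 0.63 standard errors under assumed death rates of 2% to 10%, and shrinkage of an 8.25-point difference to between 7.7 and 6.2 points under an assumed untestable share of 10% to 33%. The sign can change when losses differ between arms and does not when they are equal. Differences of one or two points against a standard error of 6.5 would not on their own be read as harm or protection, so the stronger claim that the trial would wrongly show neurotoxicity or safety is not supported. Nor do the documents require a death-or-impairment composite to replace the survivor analysis or rank above it; that is a matter of preference.

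**What to change.** Before the two-year data are analysed:

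1. Keep the analysis of cognitive and language delay among survivors.
2. State that a child who cannot be tested because of severe impairment is scored as delayed, not missing.
3. Prespecify, beside the survivor analysis, a comparison of death from any cause or neurodevelopmental impairment at 104 weeks corrected age over all randomized infants with known status. Count impairment as present when any component (cognitive or language delay, cerebral palsy, hearing loss, blindness) is present, even if another is unscored.
4. Show death and each component by arm next to the composite, with the number of unknown status.

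The cost is a few lines of analysis wording and one case report form field for the reason the test was not done; no visits or patients are added. The drawback is a composite that mixes death with impairment, which is why its components must be shown.
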